## Abstract

**Background:**

With suicide as a leading cause of death, the issue of children and adolescent suicide risks is in the spotlight today. To empower teachers in primary and secondary schools to serve as gatekeepers and to ensure the safety of children and adolescents, the systematically tailored and localized Life Gatekeeper suicide prevention program was designed for Chinese schools.

**Objective:**

With the ultimate goal of preventing child and adolescent suicide, we aim to outline a research protocol for examining outcomes of the recently created standardized school-based Life Gatekeeper program in reducing teachers’ stigma, increasing their knowledge, willingness to intervene, and perceived competence.

**Methods:**

Participants will be recruited from eligible primary and secondary schools. Cluster sampling will be used to randomly assign each school to either the intervention group or the control group. The primary outcomes are stigma against suicide, suicide literacy, perceived competence, and willingness to intervene with suicidal individuals, which will be measured using the Stigma of Suicide Scale, the Literacy of Suicide Scale, and the Willingness to Intervene Against Suicide Questionnaire, respectively. Measurements will be taken at four time points, including pre-intervention, immediately after the intervention, 6-month follow-up, and 1-year follow-up.

**Conclusions:**

The current study features innovative implementation in the real world, by using a randomized controlled trial design to examine the effectiveness of a school-based gatekeeper program among primary and secondary school teachers, following a sequence of defined and refined steps. The research will also investigate the viability of a school-based gatekeeper program for primary and secondary school teachers that could be quickly and inexpensively implemented in a large number of schools.

**Supplementary Information:**

The online version contains supplementary material available at 10.1186/s13063-024-08137-2.

## Introduction

Researchers recognize suicide as one of the most severe global public health concerns. By 2022, the global lifetime prevalence of youth active suicidal ideation and suicide attempts was 20.4 and 7.0%, respectively, according to a meta-analysis [1]. This issue has also been a matter of public concern in China. For example, a cross-sectional study found that the prevalence of suicidal ideation for primary, middle, and high school students was 30.4, 34.7, and 35.1% among 127,333 children and adolescents from several areas in China [2]. In addition, another meta-analysis study also found the prevalence of suicide attempts being 2.9% among 200,124 Chinese adolescents [3].

Suicide not only affects the long-term psychological development of children and adolescents, but it can also severely affect their family members and cause significant damage to family systems, which in turn could lead to maladaptive outcomes for children and adolescents [4, 5]. Moreover, individuals who have lost a friend to suicide often struggle with psychological distress such as depression and grief, or even suicidal ideation [6]. From a teacher’s perspective, the incident may also frequently lead teachers to develop symptoms of depression and sleep problems [7].

Recently, there has been increasing attention on the mental health of children and adolescents within the school environment, acknowledged as the “frontline of suicide prevention” [8]. Surprisingly, the mental health support available within the school system remains insufficient, which could be attributed to the ratio of 1:1360 between school psychological service providers and students in some Chinese schools [9], highlighting the concerning reality of limited access to mental health services for students. On the other hand, some at-risk students might have decreased willingness to seek professional help when struggling with mental health problems, which when combined with various effects of stigma, such as social isolation and hopelessness, may further raise their risk of suicide [10, 11]. Furthermore, the existence of some specific reasons in low-resource areas makes child and adolescent suicide more likely to be overlooked. For instance, for left-behind children, as their parents left to make a living in urban areas, their children are typically left at home with the older members of the family [12], hence these children’s ability to seek help might be hindered by the limited support from their parents. Such limitation puts an extra challenge for early identification of students at risk of suicide, hence impeding the implementation of timely interventions that could prevent the further development of suicidal risks. Therefore, there is an urgent need to establish an effective network that can increase teacher-parent-student communication to safeguard children and adolescents in low-resource areas from suicide [13].

The Gatekeeper Training (GKT) program could be a potential solution to this problem. It equips lay people with the skills to identify, assess, connect, and refer people at risk of suicide to clinicians and hospitals. This type of program could address the shortage of licensed practitioners and resources in rural areas [14–16]. For example, Question, Persuade, Refer (QPR) [17–20], Applied Suicide Intervention Skills Training [21–24], and Suicide CARE (“Careful observation,” “Active listening,” and “Risk evaluation and Expert referral” [25]) have been well-known GKTs. In addition, a systematic review of gatekeeper training for adolescent suicide prevention concluded that most GKTs had improved gatekeeper's knowledge, attitudes, self-efficacy, skills, and likelihood of intervention [26]. Overall, existing gatekeeper programs, including school-based gatekeeper training, have been found to reduce stigma, improve knowledge and self-efficacy to prevent suicide, and ultimately encourage helping behaviors among gatekeepers.

However, to the best of our knowledge, there remains a need to optimize and enrich a systematic, localized, standardized GKT program specifically designed for school teachers in China. Thus, the Life Gatekeeper Training Program has been developed to decrease suicidal behaviors among Chinese children and adolescents through teachers’ interventions. This program aims to empower school teachers to act as life gatekeepers for students experiencing psychological distress, to increase teachers’ knowledge of suicide, reduce their stigma towards suicide, and improve their skills, willingness to intervene, and perceived competence. These factors ultimately contribute to their capability as gatekeepers, which in turn could prevent child and adolescent suicide. Informed by the Theory of Planned Behavior (TPB) that shapes the program’s conceptualization, it asserts that actual gatekeeper behaviors can be anticipated by intervention intention, which is influenced by attitude, subjective norms, and perceived behavioral control [27].

Additionally, considering the high demand for communication with parents and following the most important findings from a previous Delphi study [28], this program includes a special section on teacher-parent-student communication concerning the suicidal risks of the student. Moreover, handouts for parents include a pamphlet that aims to increase the parents’ suicide literacy and hence reduce their stigma towards suicide, and an information sheet outlining mental health service resources and crisis hotlines. Overall, the training program aims to establish an effective school-family-professional institution multi-level network that protects children and adolescents from building up suicidal risks.

Meanwhile, implementing such training in the real-world setting remains a practical barrier due to the lack of human resources and expertises to spread across a large number of schools in rural areas. A strategy known as “Train-the-Trainer (TTT)” model has emerged as a potential solution, as it has been extensively employed in studies involving the distribution and implementation of novel interventions, similar to the Applied Suicide Intervention Skills Training [23]. The TTT model involves instructing individuals within a particular field on a specific subject, providing them with training and guidance on how to subsequently train, oversee, and supervise others using this approach [29]. This method is considered more viable and cost-effective for quick dissemination, although it also raises concerns regarding standardization and potential inconsistencies in training content by different trainers. Therefore, the standardized curriculum and video-based training were utilized to ensure consistent and high-quality training across different facilities and locations, as our pilot study has already been proven to be at least as effective as the traditional format of training [30].

Taken together, a systematically localized GKT was created for children and adolescents. The aim of this study was to ascertain the effectiveness of a well-established school-based Life Gatekeeper Training Program tailored for school teachers in low-resource areas. The specific focus was on enhancing teachers’ knowledge, beliefs, skills, willingness to intervene, and perceived competence in suicide prevention and was evaluated through a randomized controlled trial.

## Methods

### Trial design

The participant flow and research design are depicted in Fig. 1. This trial will be a two-arm, non-blinded randomized controlled trial (RCT) with two parallel groups: a wait-list control group and a Life Gatekeeper intervention group. All qualified teachers in the same school will be assigned to either the intervention group or the control group through cluster sampling. The day before intervention group training, participants will be required to take a baseline survey (*t*
_1_). The same day the training is finished, the post-test survey (*t*
_2_: immediately following the intervention) will be carried out. Six months (*t*
_3_) and twelve months (*t*
_4_) after the *t*
_2_ survey, respectively, follow-up questionnaires will be completed. The survey forms will be used for all polls, and the same time frame applies to the control group. The Standard Protocol Items: Recommendations for Interventional Trials (SPIRIT) standards were followed in the preparation of this manuscript (Supplementary Material 1).

**Fig. 1 Fig1:**
[figure not shown]
Participant flowchart

### Procedure

Each school will be randomly assigned to either the intervention group or the control group using cluster sampling. The researchers will inform participants of their group allocation. Participants can learn about the Life Gatekeeper training study by scanning a given QR code and then reading a detailed explanation of its purposes and procedures. All participants will be asked to provide informed consent, and the data gathered will be kept confidential. Teachers will be trained using a method referred to as the TTT model. In the Life Gatekeeper Training Program, professional instructors first conduct primary remote training for the intervention group’s core teachers. Over the week following the primary training, the intervention group’s core teachers conduct secondary in-person training for all head teachers and teaching staff from their own schools. To ensure the intervention is delivered as specified in the intervention protocol or manual, professional instructors and core teachers will complete the fidelity checklist while carrying out each training [31]. Each participant will complete the baseline survey (*t*
_1_) one day before the training of the intervention group, and the post-test survey (*t*
_2_) immediately after the training. These participants will also receive follow-up surveys at 6 months (*t*
_3_) and 12 months (*t*
_4_) after *t*
_2_. Surveys at time points 1, 2, 3, and 4 will be carried out synchronously for both the control and intervention groups. Participants in the control group, including core teachers, head of class teachers, and teaching staff, will be offered the Life Gatekeeper Training Program after the 12-month follow-up. Training certificates issued by the research team will be used to promote participant retention. Data collection training will be conducted for the team members before the study, and core teachers will also be trained to cooperate with the team members in collecting data in their respective schools. If any participant discontinues participation between baseline and the 12-month follow-up, no additional data will be collected.

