*min* minutes, *sec* seconds

All participants will also receive another package, including a training manual, an appendix, a pamphlet for parents, a pamphlet for children and adolescents, and an information sheet summarizing mental health service resources and crisis hotline numbers, in addition to these recordings. The training manual and appendix will include everything that will be covered in training. The pamphlet for parents can be used to educate parents of at-risk students about child and adolescent suicide and how to seek help. During a crisis, students can use the pamphlet for children and adolescents to find support for themselves. Meanwhile, teachers can provide at-risk students and their parents with an information sheet on mental health services and crisis hotline numbers, so that they can refer students to receive professional assistance as needed. These materials will be printed out in advance and utilized for role-plays, group discussions, and note-taking during the training. All required materials were stored in a password-protected cloud storage platform to make the materials easily accessible.

The intervention is delivered in a single day, with a break in the middle. Only members in the intervention group will have access to all resources, including video clips, as they are only available to individuals who consent to participate. Nevertheless, teachers are free to hand out the pamphlet for parents, the pamphlet for children and adolescents, and the summary sheet later in their work with at-risk students. The fidelity checklist was employed to ensure that the trainers followed each step correctly, and to guarantee consistent audiovisual delivery and adherence to the procedure.

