### Sample size calculation

Since the current study is designed to be a clustered randomization study, the sample size calculation is based on the number of clusters and the between-cluster coefficient of variation. Sample size calculation was conducted through the cpa.count function in “clusterPower” package in R. The cpa.count is a tool for computing the power, number of clusters needed, number of subjects per cluster needed, or other key parameters for a simple parallel cluster randomized trial with a count outcome [39]. The between-cluster coefficient of variation for the current study is identified as 0.01 based on the reference number defined at “carriage outcomes at 12 months in rural area” [40]. Since we aimed to capture small changes in the outcomes measure, a detectable effect size was set as *r* = 0.1 for power analysis. The number of schools fulfilling inclusion criteria in the local area was 84, which means each group will involve 42 clusters. With a power of 0.85 and alpha=0.05, the mean number of participants calculated for each cluster (school) is 30. A final sample in each group should thus achieve 1260. To account for a withdraw rate of 30%, we will recruit 1800 participants for each group. 

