### Statistical analysis

All statistical analysis will be conducted through R 4.1.0 Analyses. The primary outcomes will be conducted through generalized estimating equations modeling while controlling for all the demographic information [41]. The generalized model will be conducted to analyze the within-group and between-group differences at each time point for all primary outcomes in head-of-class teachers and education staffs. The same model will be applied to core teachers as a supplementary analysis. A 2-sided significance level will be set, and false discovery rate corrections will be applied to account for the risk of false positive generated by multiple comparisons. Descriptive statistics will be conducted for demographic information and process evaluation questions. Analyses will be conducted after the completion of post-intervention, 6-month follow-up, and 12-month follow-up data collection. Since there are no anticipated problems that are detrimental to the participant, no stopping guidelines are set.

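### Data collection ends when a teacher discontinues, with leaving the training and withdrawing from the surveys not separated; with 30% loss planned and a GEE adjusted only for demographics, the 6- and 12-month arm differences may be biased in either direction

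*Protocol article*

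**What the plan says.** The follow-up rule stands in the Procedure section of the protocol article: "If any participant discontinues participation between baseline and the 12-month follow-up, no additional data will be collected". Discontinuing is not defined further. The Intervention program section describes the training: "The intervention is delivered in a single day, with a break in the middle". Control teachers are offered it only after the 12-month survey. The Research ethics section says that participants will be advised to leave the venue if distressed, and does not say whether such a teacher counts as having discontinued.

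The abstract gives the waves: "Measurements will be taken at four time points, including pre-intervention, immediately after the intervention, 6-month follow-up, and 1-year follow-up". These are t1 to t4. The Sample size calculation section plans for loss: "To account for a withdraw rate of 30%, we will recruit 1800 participants for each group".

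Under Statistical analysis: "The primary outcomes will be conducted through generalized estimating equations modeling while controlling for all the demographic information". The contrasts follow: "The generalized model will be conducted to analyze the within-group and between-group differences at each time point for all primary outcomes". The article gives no working correlation, weighting, imputation or missing-data assumption.

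**The concern.** Three elements combine: a rule that ends follow-up at discontinuation, a large planned loss, and an analysis whose stated covariates do not include earlier outcome scores.

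The rule is a matter of conduct, so an analysis plan cannot repair it: a survey that was never sent cannot be recovered. Read literally, it could also act on one arm only. Before t4 only intervention teachers have a training day to leave or miss. If doing so counts as discontinuing, they leave follow-up, while comparable control teachers stay in.

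On the analysis side, unweighted GEE is in general valid only if loss is completely at random or depends only on covariates in the model. If teachers with low (or high) earlier scores leave more often in one arm than in the other, the 6- and 12-month contrasts compare differently selected groups. These two waves carry the evidence that any effect lasts.

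**Working it through.** **1. The plan's own figure.** 42 schools × 30 teachers = 1260 per arm, and 1260 / (1 − 0.30) = 1800, as stated. Loss at the planned rate is 0.30 × 1800 = 540 per arm, or 1080 of 3600 overall.

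**2. Assumptions for the illustration.** From the plan: 42 schools per arm, four waves, 30% loss. Assumed: 43 teachers per school (1800 / 42 = 42.9), within-teacher correlation 0.6 between waves, loss at t4 depending on the t2 score in the intervention arm only (odds ratio 1.5 or 2 per SD), and a true 12-month difference of 0.20 SD. The last matches the plan's r = 0.1 if r is read as a correlation: d = 2 × 0.1 / √(1 − 0.01) = 0.201.

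**3. Hand check under independence.** With a saturated arm-by-time mean, GEE under independence compares the observed means at t4. If retention π is logistic in a standard normal t2 score with slope b = ln(OR), the mean t2 score of those retained shifts by b × E[π(1 − π)] / E[π], which is at most b × (1 − 0.70) = 0.30b. The correlation of 0.6 carries this shift to t4.

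- OR 1.5: 0.405 × 0.30 × 0.6 = 0.073. Integrating the expectation exactly gives 0.071.
- OR 2: 0.693 × 0.30 × 0.6 = 0.125. Exact integration gives 0.114.

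**4. Simulated 12-month bias, by working correlation (SD units).**

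| Working correlation | OR 1.5 | OR 2 |
|---|---|---|
| Independence | about +0.07 | about +0.11 |
| Exchangeable by school, ICC 0.01 | about +0.06 to +0.07 | about +0.11 |
| Exchangeable by school, ICC 0.05 | about +0.06 | about +0.10 |
| Exchangeable by teacher | about 0 | about 0 |

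**5. Why the school level gives little protection.** A school supplies 43 × 4 = 172 observations, so 172 × 171 / 2 = 14,706 pairs. Only 43 × 6 = 258 of them (1.75%) are within a teacher. The single exchangeable correlation is then about 0.0175 × 0.6 + 0.9825 × 0.01 = 0.02 at ICC 0.01, and 0.0175 × 0.6 + 0.9825 × 0.05 = 0.06 at ICC 0.05. Both are far below the 0.6 that links a teacher's own scores.

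**6. Other dropout patterns.** A second simulation let dropout before t3 and before t4 depend on the previous score, with 30% lost overall and Monte Carlo error about 0.007. The 12-month bias under independence was:

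- 0 when loss was completely at random, and 0 with equal dependence in both arms and no arm effect;
- about −0.05 to 0 with equal dependence and arm effects present;
- +0.11 with dependence in the intervention arm only;
- −0.25 with opposite dependence in the two arms.

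Adding the baseline score as a covariate reduced the last two to +0.05 to +0.09 and −0.13. Modelling within-teacher correlation, exchangeable or unstructured, kept every case within about 0.015.

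**The case against.** The article does not say that the GEE is an available-case analysis or that it uses independence. A condensed article may leave working correlation and missing-data handling to an analysis plan, and one that models within-teacher correlation would remove almost all of the simulated bias. This stands: the risk is conditional and is not a general property of GEE. With such a structure, moving to a mixed model would be largely a matter of preference.

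The wording of the rule most naturally means leaving the study. Training takes one day, so most discontinuation over a year can only be loss from the surveys, where ending collection is usual. This also stands. What remains is that the text does not exclude the other reading.

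The simulation makes loss depend on the t2 score, whereas a teacher who leaves the training may have no t2 score. That is fair. The figures describe later survey loss. For teachers who leave training, the direct remedy is to keep sending the surveys.

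Three stronger readings are tempting, and the documents support none of them.

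- A reader might infer that the bias favours the programme. Its sign depends on who leaves and in which arm: reversing the assumed dependence at OR 1.5 turns a true 0.20 into about 0.20 − 0.07 = 0.13.
- A reader might infer from "Training certificates issued by the research team will be used to promote participant retention" that the incentive reaches the arms at different times. No issue date is given, and issue after follow-up fits the sentence as well.
- A reader might take the 30% as evidence that loss is not at random. It is a recruitment allowance and says nothing about mechanism.

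**Conclusion.** The point holds as a conditional risk. The follow-up rule is ambiguous in a way that could remove teachers from one arm only, and the stated analysis adjusts for demographics but not for earlier scores. With 30% loss, the 12-month difference could be off by about 0.06 to 0.11 SD under the assumed intervention-only dependence, if the working correlation is independence or exchangeable by school. Against a true 0.20 SD that is 30% to 55% (0.06 / 0.20 and 0.11 / 0.20). The bias is about zero if within-teacher correlation is modelled, and it largely cancels if dependence is the same in both arms.

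Apart from the 42 schools, the four waves and the 30%, every input is an assumption. Neither the existence nor the direction of bias in this trial is established. The change is still worth making: schools are the randomised unit, so clustering the GEE on school is a natural choice, and it is one that leaves the contrast exposed.

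**What to change.** 1. **Follow-up rule.** Define discontinuation. State that teachers who leave or miss training stay in follow-up and are sent the remaining online surveys unless they withdraw consent to data collection.
2. **Primary analysis.** Make it use the earlier scores of those lost. One way is a model with both teacher and school correlation, for example a linear mixed model with both random effects. The other is multiple imputation that respects schools and uses t1 to t3 scores before the GEE. Keep the GEE on observed data as a sensitivity analysis.
3. **Reporting.** Give loss by arm at each wave.

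The cost is some added analysis work and reliance on missing at random, which cannot be verified. Sending further surveys is cheap because they are online, but the first change can affect only waves not yet collected. The Trial status section reports recruitment closed by March 2023, the second follow-up collected as of September 2023, and the final follow-up expected to end by March 2024. The second and third changes can be made whatever the stage of collection, and should be fixed before the 12-month data are analysed.
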